## Abstract

**Background:**

A large number of practices used in health care lack evidence of effectiveness and may be unnecessary or even cause harm. As such, they should be de-implemented. While there are multiple actors involved in de-implementation of such low-value care (LVC) practices, ultimately, the decision to abandon a practice is often made by each health care professional. A recent scoping review identified 6 types of factors affecting the utilization vs. abandonment of LVC practices. These factors concern health care professionals, patients, outer context, inner context, processes, and the characteristics of LVC practice itself. However, it is unclear how professionals weigh these different factors in and how these determinants influence their decisions about abandoning LVC practices. This project aims to investigate how health care professionals account for various factors as they make decisions regarding de-implementation of LVC practices.

**Methods:**

This project will be carried out in two main steps. First, a factorial survey experiment (a vignette study) will be applied to empirically test the relevance of factors previously identified in the literature for health care professionals’ decision-making about de-implementation. Second, interactive workshops with relevant stakeholders will be carried out to develop a framework for professionals’ decision-making and to offer suggestions for interventions to support de-implementation of LVC practices.

**Discussion:**

The project has the potential to contribute to improved understanding of the decision-making involved in de-implementation of LVC practices. We will identify which factors are more important when they make judgments about utilizing versus abandoning LVC practices. The results will provide the basis for recommendations concerning appropriate interventions to support de-implementation decision-making processes.

**Supplementary Information:**

The online version contains supplementary material available at 10.1186/s43058-021-00153-6.

Contributions to the literature
This project will contribute to de-implementation research by offering valuable insights into health care professionals’ decision-making when they deal with the dilemma of de-implementing low-value practices.This study will apply a vignette survey experiment to empirically test which factors influence professionals’ judgments about utilizing vs. abandoning low-value care practices.The project will provide theory-based intervention suggestions to support de-implementation of low-value care practices.

## Background

Health care organizations face demands to provide high-quality care and use their resources efficiently. Yet, practices with limited evidence for their benefits keep being prescribed and utilized [1]. The problem is that, on the one hand, it takes a long time to produce research evidence and get it to practical use [2]; on the other, the knowledge quickly becomes outdated and inaccurate when new findings emerge that contradict previous ones [3]. As a consequence, many practices currently used in health care may be unnecessary, ineffective, or even harmful. Hereafter, these non-recommended, ineffective, or harmful practices are referred to as low-value care (LVC). To increase health service efficiency, researchers and practitioners have increasingly turned their interest towards de-implementation [4], i.e., the process of abandoning practices that are not evidence-based [5]. However, the focus has primarily been on *what* should be abandoned, not *how* it should be done. Thus, while lists of non-recommended practices have become common (e.g., Choosing Wisely [6] or the Swedish National Board of Health and Welfare’s “not to do” label in the guidelines), they have little chance of leading to improvements without sufficient knowledge about efficient de-implementation—that is, translating the *what* should be de-implemented into *how* this should actually be carried out [5, 7, 8].

There are multiple actors dealing with LVC and its consequences [9]: national, regional, and organizational health care governance systems [10]; professionals [11]; patients and their associations [12]; and the wider public. Yet, at one point, the ultimate decision to do or not do something is placed in the hands of each health care professional. A survey among physicians demonstrated that they feel great responsibility to make sure their patients avoid unnecessary tests or procedures; overwhelmingly, these physicians also believed that they are in the best position to address the problem, with government agencies ranking far behind [11]. Thus, how and why health care professionals make judgments about using or abandoning a certain practice on the spot in their offices demands attention. Multiple factors influence health care professionals’ decisions. A recent scoping review concerning determinants for the use and de-implementation of LVC in health care identified 6 types of factors concerning: health care professionals, patients, outer context, inner context, process, as well as evidence and LVC practice. Thus, the decision is likely to be influenced by factors across system levels. First, LVC practices have been concerned with healthcare professionals’ individual characteristics and preferences. Particularly, individuals who have invested their time and knowledge in a certain practice may experience a de-implementation process as emotionally demanding. Care practices can be deeply attached to position, status, values, and identity, touching upon issues like what is considered relevant knowledge, as well as ethics and professional roles and expectations. Identified determinants also included professionals’ fear of malpractice. For example, the risk of exposing patients to unnecessary radiation in LVC imaging was perceived to be less significant than the risk of missing a diagnosis [13].

Second, professionals’ use of LVC is also influenced by patient preferences and wishes. In fact, patient requests seem to be a stronger factor for de-implementation compared to implementation of new evidence [14]. For instance, over half of US physicians reported that they would order tests if they were requested by a patient even if they knew these tests were unnecessary [11]. Patient knowledge may act both as a facilitator and a barrier to de-implementation of LVC. When patients are aware of the negative consequences of a specific LVC practice, they are more likely to discuss alternative treatment [15].

Third, professionals’ use of LVC is also determined by factors in the outer context of health care, such as social, political, and geographical factors. For example, the scoping review revealed that in the majority of the studies, having private health insurance was linked to receiving some LVC practices, when compared to other insurance types [14]. Steering mechanisms, including financial aspects, strongly influenced what practices were used, especially when a pay-for-performance system was applied [16]. There is a risk that professionals are encouraged to choose practices based on reimbursement levels rather than the scientific evidence. The review also showed that a policy concerning restricted LVC use was linked to its lower utilization, while advertising about drugs and treatments was identified as influencing more use of LVC.

Fourth, inner context factors such as structural and social environments of hospitals, clinics, and care centers are also determinants of LVC and may influence professionals’ decisions. For example, a lack of care continuity (e.g., having several care providers) was linked to a higher use of LVC practices [14]. Structures in the organization that facilitated using LVC, such as the ownership of equipment used for a particular LVC practice and the ease with which LVC lab tests can be ordered, have also been shown to increase the probability of LVC, along with factors such as reduced support in decision making due to, e.g., absence of teamwork, individual rather than clinic-based decision making, or a lack of feedback/accountability.

Fifth, factors relating to processes of managing LVC may influence decisions about de-implementation, including complexity of a de-implementation process, having routines for managing LVC issues (such as meetings or communication with care recipients [17]), or managerial goals related to lowering LVC. Finally, the characteristics of the scientific evidence undeniably impact how professionals make decisions on whether to provide or abandon a low-value practice. This has to do with how clear the evidence for the low-value practice was and whether an alternative practice is available [18]. Conflicting guidelines and inappropriate or inapplicable guidelines for the patient group also lead to more LVC [14]. Furthermore, physicians’ uncertainty in interpreting research findings and difficulty relating those findings to their own situations contribute to using LVC [19].

In sum, professionals make decisions to de-implement a practice based not only on current evidence but also contingent on patient expectations and characteristics, a wider economic and policy context, prevailing rules, and finally their own knowledge, attitudes, and behaviors. Most prior studies have focused on listing the determinants (i.e., what factors predict provision of LVC) rather than scrutinizing exactly *how* professionals weigh these factors and how these factors impact decisions that either lead to the abandonment or continuation of a LVC practice. Thus, there is lack of knowledge on how professionals carry out decision-making processes concerning providing or abandoning a LVC practice. Focusing on individual decision-making is relevant because health care professionals tend to have considerable autonomy to make decisions as part of their daily work practice. This autonomy may become a source of tension that professionals in health care deal with [20]. On the one hand, the organizations provide highly scripted regulations and goals to professionals, but on the other hand, professionals also need to be responsive to individual cases. They need to navigate this quandary given the boundaries of their professional values and the available organizational resources. In fact, according to the theory of street-level bureaucracy [20], professionals in welfare organizations often lack the necessary resources (e.g., time, information) to provide the highest quality services to each client. Professionals manage this by creating routines and practices and psychologically simplifying both the clients and their environment.

Given the crucial role of health care professionals’ judgments in the de-implementation process, there is a need to test which of the abovementioned factors influence their decision-making related to LVC practices to the highest extent. Overall, one of the main knowledge gaps related to de-implementation deals with understanding professionals’ judgments for solving the potential tension between scientific knowledge and pressure from different actors and aspects of the health care system. Quantifying how factors influence decision-making—both independently and jointly—may offer valuable contribution to practice. Specifically, it may allow development of the best practices for de-implementation processes, identifying barriers, and designing continuing education.

### Aim and research questions

The purpose of this project will be to (1) experimentally test which determinants influence the probability of utilization vs. abandonment of LVC practices most and (2) develop a conceptual framework for professionals’ decision-making about LVC practices to support de-implementation. The following research questions (RQs) will be answered:
How do professionals balance and make trade-offs between the distinct determinants, such as their individual characteristics, patient factors, processes as well as health care system inner and outer context, and finally the LVC practice itself?How can professionals’ decision-making to abandon LVC be facilitated at different health care system levels (organizational, regional, and national)?

## Methods

### Overview

This project will be carried out in two main steps. First, a factorial survey experiment (FSE) design [21]—also known as a vignette experiment—will be applied to test how professionals carry out decision-making processes while considering multiple factors that are likely to affect their decisions. This step will be preceded by a pilot study consisting of group interviews where relevant tensions for decision-making will be identified for each group of health care professionals to inform the content of the vignettes.

In the second step, we will develop a conceptual framework for professionals’ decision-making concerning de-implementation and prepare corresponding intervention suggestions. The FSE results, together with the results from relevant literature reviews [14, 22] and group interviews, and a theoretical approach (i.e., theory of street-level bureaucracy) will be used to gradually shift from an intensive focus on how de-implementation decisions are made to the potential solutions to improve the process.

The research will be conducted within primary health care in Sweden. Swedish primary health care is part of the tax-funded health care system and is governed by 21 regions [23]. Several different professional groups work at Swedish primary care centers, which makes it a promising environment to conduct this research. Potential respondents will consist of the following professional groups in primary care: nurses, physicians, physiotherapists, and psychologists. The recruitment of research participants across the two steps will be performed in collaboration with an R&D partner from Stockholm: Academic Primary Care Center (APC). The APC operates in close collaboration with primary care, as well as universities and research institutes. It aims to contribute to quality assurance and development of primary care for staff and students in the Stockholm Region. This collaboration will ensure that the research meets the needs of the primary care and that the project will be well anchored in the organization.

Additional file 1 presents the STROBE checklist [24] of items included in this protocol.

### Study 1

#### Design

A cross-sectional factorial survey experiment will be conducted to investigate the decision-making process of health care professionals concerning potential LVC practices. This approach combines survey research with experimental research [21, 25]. Here, the professionals are asked to make multiple decisions based on random generation of the vignettes (i.e., concrete, fictive clinical case descriptions [21]). An FSE allows analyses of professionals’ judgments and is particularly suitable for investigating complex situations with multiple stimuli. This approach has the unique ability to simultaneously measure the independent effects of respondents and situational factors without the need to give participants every possible combination of variables. This method is widely used to study health care professionals’ decision-making, e.g., [26–29]. FSE is a suitable method to study the often, and somewhat, sensitive issue of LVC because it provides a less personal and therefore less threatening way of exploring the topic [21]. Furthermore, professionals’ decision-making is often challenging to study with conventional social science methods such as interviews and observations [21]. Although the decisions made in an FSE are hypothetical and do not replicate real life, it is considered suitable for providing an in-depth insight into decision-making processes, which this project aims to do. Apart from manipulating the factors in the vignettes, we will collect relevant data about health care professionals, which may affect how they make their decisions. Following the previous literature [14, 30], we will consider their length of clinical experience, fear of possible litigation, and a tendency to worry that they may miss a certain diagnosis. For the sensitivity analysis, we will control gender.

#### Study materials—vignettes

Based on a recent scoping review summarizing factors affecting de-implementation [14], we will identify potential tensions in decision-making processes among health care professionals. Tensions consist of situational attributes that together constitute a potential dilemma for a professional. For instance, a tension can be a situation where a low-value practice is strongly requested by a patient and there are low costs related to providing it, but the evidence is clear that it has no clinical benefits. The factors identified in the literature will be discussed with the R&D partner to validate the ecological validity of the material. Thereafter, we will create drafts for vignettes, i.e., descriptions that comprise a series of sentences in a fixed order containing the relevant dimensions for a certain decision (see Table 1 for examples of dimensions and their values).

**Table 1 Tab1:** Vignette dimension examples and their values

Dimension example	Variable values
Patient expectation	1. Strongly demands practice
	2. Neutral about practice
	3. Strongly against practice
Patient’s age	1. Young adult
	2. Middle-aged
	3. Elderly
Cost of the practice	1. Low
	2. High
Trust towards the source of the guideline identifying practice as LVC	1. Yes
	2. No
Evidence for the lack of benefits of the LVC practice	1. Clear
	2. Unclear

The level or presence of a certain dimension (e.g., patient wishes for a certain practice) is randomly varied among the vignettes and respondents (see Fig. 1). These vignettes present a story that is relevant for a specific profession, although the tensions included can be similar among professional groups (i.e., patient requests and costs in relation to evidence).

**Fig. 1 Fig1:**
[figure not shown]
Randomly populated vignette example

Following the recommendations for FSEs, we will use approximately 7 ± 2 dimensions with 2–3 levels for each of these [21, 25]. In this way, we will be able to empirically test how differences in the dimensions impact the participants’ decisions (e.g., a low-value practice is strongly OR not at all required by a patient, low OR medium OR high costs are related to providing it, and the evidence is clear OR unclear for the lack of clinical benefits). Judging several similar, but not identical, situations by each respondent allows the FSE to decompose the structure of the individuals’ answer behaviors and thereby uncover the impact of the different factors [21]. The dependent variable will be the respondent’s decision to provide the practice described in the vignette, using a visual analog scale from 0% (extremely unlikely) to 100 % (extremely likely).

The vignette universe will be generated by crossing all of the possible combinations (Cartesian product) of the vignette dimensions’ categories to ensure orthogonality across the factors [21]. The experimental design (i.e., vignette universe) will be divided into different decks (blocks) presented to different respondents. This way, we will be able to use a larger overall number of vignettes to enhance statistical efficiency [21]. For blocking to decks, we will use deliberate blocking techniques based on design efficiency (D-efficiency) [21]. A minimum of five respondents will assess each deck [21]. We will use the SAS macro “%mktblock” to ensure a randomized distribution of the whole vignette universe over the decks in order to attain maximum statistical efficiency. By distributing the different questionnaires as evenly as possible, we will ensure that the correlations between dimensions are close to 0 and not significant.

The drafts for vignettes will be pilot-tested and further developed in the group interviews with a selection of professionals from the participating primary care centers [31]. Thus, the clinical relevance of the tensions and factors will be further tested. This is a crucial step as the strength of the methodology used in the next project step relies on how well the respondents identify with the situations described in the vignettes [21]. Use of professionals’ expertise is a common way to ensure that the vignettes represent the realities these are portraying and, in this way, increase the validity of the methodology [21]. We will use a purposeful sample that varies in terms of gender and length of profession. This diversity seeks to increase the relevance of the vignettes. The group interviews will start with a presentation of the vignette drafts, which thereafter will be discussed by the participants. The moderator will pose questions about the formulation of the vignettes, their relevance, and other potential factors that might impact decision-making. The group interviews will continue until saturation is achieved within each professional group. We estimate that approximately 2–3 group discussions for each professional group are needed, for a total of 8–12 group interviews. To finalize the vignettes, a smaller number of professionals will be consulted for a cognitive pretest based on think-aloud techniques [28]. They will be asked to read the vignettes with the different dimensions and levels to check whether these are easy to read and understand.

#### Participants and procedure

First, managers for each primary care center will be approached to anchor the project and to obtain approval for the professionals’ participation. Based on our previous experiences conducting surveys with an organization, we estimate that at least 60% of the centers will participate (i.e., at least 42 centers). The number of professionals at each center varies, commonly from 15 to 20. This estimate would give us a population of professionals that is large enough for the planned survey (at least 630–840 individuals, estimated response rate 60%) [21], although a more thorough power calculation will be performed when the vignettes have been finalized, i.e., the number of factors and dimensions is determined. SAS software will be used for the power analysis. We plan to use quota sampling as our sampling technique and multiple regression analyses for the data analysis. Although simple randomization is common, the current FSE literature proposes that quota sampling has advantages in understanding confounded parameters. We will, therefore, based on the results of the literature review, investigate whether a specific characteristic in the respondent population (e.g., gender) can be an appropriate factor for stratification in a quota sampling. Otherwise, we will use random sampling and carefully target the potential limitations of this method.

Each survey respondent will answer 9–12 vignettes. This number was determined based on prior research showing that health care professionals are able to provide reliable answers to this number of vignettes [21, 26, 29]. The number of vignettes will be based on the time the participant are estimated to be able to spend on the survey (max. 15 minutes), the difficulty and complexity of the vignettes and statistical considerations (e.g., power) [21].

#### Statistical analysis

Because each respondent will evaluate multiple vignettes, this implies a hierarchical data structure in which the responses (decisions to provide the LVC practice in each scenario) are nested within respondents (healthcare professionals). To address this violation of the classical regression assumption of uncorrelated error terms, mixed-effects models will be performed with vignettes’ dimensions as level 1 and respondents as level 2. First, a random intercept-only model with no predictors (i.e., null model) will be performed to calculate an intraclass correlation coefficient (ICC) and to benchmark model fit. Then, vignette dimension variables and respondent variables, as well as their interactions, will be added sequentially. In the case of low ICC coefficients, regular multivariable regressions will be performed alongside multilevel analyses for a sensitivity test.

### Study 2

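### The two-level model has no term for primary care centre although respondents are recruited through centres, so standard errors for the non-randomised respondent variables may be modestly too small

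*Protocol article*

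**What the plan says.** Under Methods, Study 1, Participants and procedure, the centre is the route into the sample: "managers for each primary care center will be approached to anchor the project and to obtain approval for the professionals’ participation". The article expects at least 42 centres to take part. On their size it says: "The number of professionals at each center varies, commonly from 15 to 20". The resulting population is given as "at least 630–840 individuals, estimated response rate 60" per cent, and on the rating task: "Each survey respondent will answer 9–12 vignettes".

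Under Statistical analysis, the only nesting described is that of ratings within respondents. The mixed model takes vignette "dimensions as level 1 and respondents as level 2". Vignette variables, respondent variables and their interactions are then added in sequence. If the ICC is low, ordinary multivariable regression is run alongside as a sensitivity test. No centre random effect, centre fixed effect or centre-clustered variance appears in either analysis.

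The Background gives a reason to expect colleagues at one centre to answer alike: "inner context factors such as structural and social environments of hospitals, clinics, and care centers are also determinants of LVC".

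**The concern.** The article introduces the mixed model to deal with correlated errors, but covers only one of the two sources that its sampling creates. Ratings cluster within respondents, and respondents cluster within centres. Colleagues share equipment, ordering routines, teamwork and feedback, which the Background lists among the influences on low-value care.

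If respondents' average ratings are correlated within a centre, a model with respondents as its top level treats colleagues as independent. Estimates for variables that are not randomised within respondents then look more precise than they are. The planned variables exposed to this are length of clinical experience, fear of litigation and worry about missing a diagnosis, with gender in the sensitivity analysis. The single ICC from the null model would also merge between-centre with between-respondent variance, so it could not show whether the centre matters.

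**Working it through.** **Inputs from the article (Participants and procedure).** At least 42 centres, being 60% of those approached; 15–20 professionals per centre; 60% response; 9–12 vignettes per respondent.

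**The article's own figures.** 42 × 15 = 630 and 42 × 20 = 840, so the stated population reproduces exactly. 42 / 0.60 = 70 centres approached.

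**Respondents per centre.** Reading 630–840 as those invited: 0.60 × 630 = 378 and 0.60 × 840 = 504 respondents. Then 378 / 42 = 9 and 504 / 42 = 12 per centre.

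**Assumed, because the article gives no value.** Centre ICC of respondents' mean ratings, ρ_y, 0.02–0.10. Centre ICC of a respondent covariate, ρ_x, 0.1–0.3.

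**Formulas**, with m respondents per centre:
- Respondent covariate: DE = 1 + (m − 1) × ρ_y × ρ_x.
- Overall mean or centre-constant variable: DE = 1 + (m − 1) × ρ_y.
- Actual type I error of a nominal two-sided 5% test: 2 × [1 − Φ(1.96 / √DE)].

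**Results**

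| Target | Low end (m = 9, ρ_y = 0.02) | High end (m = 12, ρ_y = 0.10) |
|---|---|---|
| Respondent covariate | ρ_x = 0.1: 1 + 8 × 0.02 × 0.1 = 1.016; 5.2% | ρ_x = 0.3: 1 + 11 × 0.10 × 0.3 = 1.33; 8.9% |
| Overall mean or centre-constant variable | 1 + 8 × 0.02 = 1.16; 6.9% | 1 + 11 × 0.10 = 2.10; 17.6% |

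**The other reading.** The wording does not settle whether 630–840 already allows for non-response. If they are the respondents, m is 15–20. For a respondent covariate, DE then runs from 1 + 14 × 0.02 × 0.1 = 1.03 to 1 + 19 × 0.10 × 0.3 = 1.57 (about 5–12%). For a centre-constant variable it runs from 1 + 14 × 0.02 = 1.28 to 1 + 19 × 0.10 = 2.90 (about 8–25%).

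**Simulation check.** 42 centres × 12 respondents × 10 vignettes, 2,000 runs, respondents as the top level. The Monte Carlo standard error at 5% is √(0.05 × 0.95 / 2000), about 0.5 percentage points.

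| Centre share of between-respondent variance | Vignette dimension | Respondent covariate (ρ_x = 0.10) | Centre-constant variable |
|---|---|---|---|
| 0 | 4.6% | 5.6% | 4.8% |
| 0.05 | 5.4% | 5.2% | 11.6% |
| 0.10 | 5.1% | 5.0% | 16.6% |

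Randomised vignette effects hold their level. A weakly clustered respondent covariate shows no detectable inflation; the formula predicts only a small one there (m = 12, ρ_y = 0.10, ρ_x = 0.10: DE = 1.11, 6.3%). Only the centre-constant variable is clearly affected. In one further run (centre share 0.05), vignette effects were allowed to vary between centres with an assumed slope SD of 0.1, and their type I error rose to 11.5%.

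**The case against.** The strongest reply is that the main result is safe. The first aim is experimental, and the vignette dimensions are randomised across vignettes and respondents. A reader might infer that the missing centre level undermines the vignette findings. The article does not support that: centre differences in overall level largely cancel within respondents, and the simulation agrees. The exception, vignette effects that differ by centre, is an added assumption.

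A reader might also attach the 7–18% figure to the planned tests. It applies to overall means or centre-constant variables, and the article names no such analysis. For the variables it does name the range is 5–9%, and the upper end needs both assumed ICCs at their highest.

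A third tempting reading is that the two-level model leaves the second research question, on facilitating decisions at organisational level, unanswerable. That question is addressed mainly in Study 2, through a conceptual framework and workshops that draw on Study 1 as one source among several. Nothing says it will be answered by partitioning variance between centres.

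Clusters may also be smaller. Vignettes are specific to a profession, there are four professions, and the article does not say whether the models are pooled. With separate models and an equal split, 9–12 per centre becomes 2.25–3. Even a centre-constant variable then has DE of only 1 + 1.25 × 0.02 = 1.03 to 1 + 2 × 0.10 = 1.20, or about 5–7%.

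These points limit the size and reach, and they stand. The last reply, that a further random term is a detail left to a fuller plan, is weaker. The article does not leave the hierarchy open: it names the levels and stops at two, and its fallback regression has no centre term either.

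**Conclusion.** The point holds in a limited form. The stated model does not match the stated sampling, and the article itself gives grounds to expect correlation within centres. The consequence is a possible, modest understatement of standard errors for the non-randomised respondent variables: a design effect of about 1.02–1.33 and type I error of about 5–9% under the assumed ICCs with 9–12 respondents per centre. It would be somewhat larger if 630–840 are already the respondents, and smaller if models are fitted by profession or the covariates vary almost wholly within centres. With no centre ICC in the article, a material effect is possible but not shown. The larger figures become relevant only if overall means or centre-constant variables are reported. The main vignette comparisons are not called into question on this ground.

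**What to change.** - Record a centre identifier for every respondent at data collection; it may not be recoverable later.
- Add a random intercept for centre, giving ratings within respondents within centres, or keep two levels and use centre-clustered standard errors. Cluster on centre in the single-level sensitivity regressions too.
- Report the null-model ICC separately for respondent and centre. If the centre component is near zero, the two-level model is then justified by the data.
- In the deferred power calculation, allow for a centre ICC where it concerns respondent-level effects.

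A centre random intercept does not cover vignette effects that vary by centre. If that is thought plausible, centre-clustered standard errors or a random slope would be needed.

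The cost is one identifier, one extra variance term and slightly wider intervals for respondent-level effects.
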